**Figure 1 F1:**
[figure not shown]
Project overview. BTD = Shi's Yi-Qi Bu-Shen Tong-Luo decoction, DRF = distal radius fracture.

### Data collection and monitoring

2.15

All participants will receive treatment of manipulation plus BTD or BTD placebo for 4 weeks and followed-up for another 8 weeks. Two statisticians independently will record 4 rounds of disease assessments (the baseline, week 2, week 4, and week 12) and 2 rounds of safety assessments (the baseline and week 4) in Epidata software (Version 3.1). Disagreement will be solved by discussion with a third statistician.

### Quality control

2.16

Huangpu Branch, Shanghai Ninth People's Hospital affiliated to Shanghai Jiaotong University control the quality of this whole search. Training will be conducted to study the process of the entire trial before the trial. All the physicians, therapist and evaluators will receive this training together. A specific investigator will check the CRFs weekly to make sure the study quality.

### Sample size calculation

2.17

Sample size was calculated according to the Cooney wrist score, based on previous studies (Zhang et al 2014^[10]^). 

 was used, N1 and N2 mean the patient numbers in BTD group and placebo group; 

 when *α* = 0.05; 

 when 1-*β* = 0.90; *σ* (standard deviation of 2 groups) = 7.7; *k* = 1; 

 (the difference of Cooney wrist score in BTD and placebo group) = 4; Δ = 0. Therefore, we decided to include 80 patients in the study (40 of them in each group).

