### Randomization and allocation

2.9

The random number list will be generated through Statistical Packages of Social Sciences (SPSS) software (version 24.0) in a 1:1 ratio by a trained statistician. The list contains both the sequence number of inception and the group of BTD or BTD placebo. This statistician will contact and provide the randomization list for medicine pharmacy of Huangpu Branch, Shanghai Ninth People's Hospital affiliated to Shanghai Jiaotong University. Medicine pharmacy will produce the medicinal liquid and paste the sequence number label on plastic bags of BTD or placebo as the list.

The statistician and pharmacy will preserve the randomization list to maintain concealment. And the other investigators will be unable to know the sequence numbers and group of each participate until the trial completed. Medicine with labels will be stored in a locked and individual room. A trained administrator will charge the medicine and the key.

When a participant will be recruited in, the investigator will make a central telephone call and give him/her the medicine (BTD or the placebo) from the administrator.

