##### Cooney wrist score (from baseline to week 4)

2.12.1.1

The Cooney wrist scoring system used for the assessment and functional evaluation of the wrist. It includes 4 parts, pain symptoms (25 points), functional status (25 points), grip strength (25 points), range of motion (25 points). The total score of Cooney is 100 points. The higher Cooney score, the better recovery of wrist function. The evaluation criteria is: excellent, 90 to 100 points; good, 80 to 89 points; fair, 65 to 79 points; poor, 0 to 64 points (details in Table 3).

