### Statistical analysis

2.18

All data analyses will be accomplished using SPSS software (version 24.0). Continuous data are presented as mean ± standard deviation and categorical data as frequencies. Continuous variables following the normal distribution will be analyzed by Student *t* test; otherwise, nonparametric tests will be used to compare group differences. Statistical test is 2-sided and *P*-value <.05 will be defined as statistically significant. We will adopt multiple imputation to handle missing data statistically. A subgroup analyses will be conducted when necessary. Intention-to-treat approach and last-observation-carried-forward method will be applied to deal with the missing values.

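### The stated sample-size inputs require 78 patients per group for 90% power; the planned 40 per group gives about 63%.

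*Protocol article*

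**What the plan says.** Section 2.17 (Sample size calculation) bases the sample size on the Cooney wrist score, whose change to week 4 is the primary outcome (2.12.1.1, "Cooney wrist score (from baseline to week 4"). It gives the significance level ("when *α* = 0.05"), the power ("when 1-*β* = 0.90"), the spread ("standard deviation of 2 groups) = 7.7"), the difference to detect ("the difference of Cooney wrist score in BTD and placebo group) = 4"), an allocation constant k of 1 and a margin Δ of 0. It concludes: "Therefore, we decided to include 80 patients in the study (40 of them in each group". Section 2.9 confirms equal allocation ("in a 1:1 ratio by a trained statistician"). Section 2.18 fixes the sidedness ("Statistical test is 2-sided") at the 5% level, and names the Student t test, or a nonparametric test where normality fails.

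**The concern.** A 4-point difference with a standard deviation of 7.7 is a standardised effect of 4 / 7.7 = 0.52. Forty patients per group is too few to detect an effect of that size with 90% power. The paragraph presents 80 as the result of its inputs, not as a feasibility limit, so the reader is told that the trial has 90% power for 4 points on its primary outcome. If it has much less, a real 4-point benefit has a substantial chance of being missed, and a non-significant result would carry more weight against the decoction than the data can support.

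**Working it through.** **Inputs.** From 2.17: α = 0.05, power 0.90, SD 7.7, difference 4, Δ = 0, k = 1. From 2.18: two-sided test. The printed formula and z-values are not legible in the text at hand. The listed symbols are those of the standard superiority comparison of two means, which is used here:

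n per group = (1 + 1/k) × (z for α + z for power)² × SD² / (difference − Δ)²

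**Trying to reproduce 40 per group**

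- Two-sided 5%, 90% power: 2 × (1.960 + 1.2816)² × 7.7² / 4² = 2 × 10.507 × 59.29 / 16 = 77.87, so **78 per group, 156 in total**. The exact t calculation gives 78.85, so 79 per group, 158 in total.
- One-sided 5%, 90% power: 2 × (1.645 + 1.2816)² × 59.29 / 16 = 63.47, so 64 per group.
- Two-sided 5%, 80% power: 58.17, so 59 per group.
- One-sided 5%, 80% power: 45.82, so 46 per group.

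None of these gives 40. Leaving out the factor (1 + 1/k) = 2 from the first line gives 10.507 × 59.29 / 16 = 38.94, so 39 per group or 78 in total, which is close to the plan's 40 and 80. Taking the per-group 78 as the total and rounding up leads to the same place. Either would explain the figure, but the document states neither.

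**Power with 40 per group**

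- Standard error of the difference: 7.7 × √(2/40) = 1.722.
- Difference in standard errors: 4 / 1.722 = 2.323.
- Normal approximation, two-sided: Φ(2.323 − 1.960) = Φ(0.363) = 64.2%.
- Noncentral t, two-sided: **63.1%**.
- One-sided 5%: 75.1% (normal) or 74.5% (t).

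**What 40 per group can detect (two-sided 5%)**

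- With 90% power: 1.722 × (1.960 + 1.2816) = 5.58 points by normal approximation, 5.65 by t test.
- With 80% power: 4.88 points by t test.
- For 4 points with 90% power, the SD would have to be about 5.5 instead of 7.7.

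**The case against.** The printed formula is missing from the text at hand, so nobody can see from it whether the factor of 2 was dropped or a total was mistaken for a group size. That is fair as regards the cause, which remains conjecture. It does not rescue the number, because every numeric input is printed and no standard two-group version of the formula turns them into 40 per group.

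A second defence is that baseline adjustment could recover the lost precision. The article plans only a t test or a nonparametric test and states no correlation. The gain also depends on what 7.7 measures, which 2.17 does not say. If it is the SD of the week-4 score, a baseline correlation r multiplies the variance by 1 − r², and r = 0.7 brings power at 40 per group to about 89.5%. If it is the SD of the change, adjustment multiplies the variance by (1 + r)/2 (equal variances assumed), and r = 0.7 gives only about 70%. Adjustment is therefore a possible help and no assurance of 90%.

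Third, the article gives no dropout allowance, but an article may leave that to the full protocol, so its absence is not counted here. For scale only: an assumed loss of 5% to 20% (38 down to 32 per group) would lower t-test power to about 61% to 53%; at 10% (36 per group) it is 58%. The shortfall exists with no loss at all.

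**Conclusion.** The concern holds. On the plan's own inputs, 80 patients is about half of the 156 needed (158 by t test), and power for the primary comparison is about 63%, not 90%. The chance of missing a true 4-point benefit is about 37%, against the 10% implied. This rests on the SD of 7.7 and the difference of 4 as printed, equal groups, the two-sided 5% test of 2.18, an unadjusted comparison and complete data. Reading the calculation as one-sided would contradict 2.18 and still leave power at about 74%. The error concerns the headline design claim for the primary outcome and has to be corrected.

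**What to change.** Restate section 2.17: with 40 per group, SD 7.7 and a two-sided 5% t test, the trial has about 63% power for a 4-point difference, 80% power for about 4.9 points and 90% power for about 5.7 points, before any loss to follow-up. Say whether 7.7 is the SD of the week-4 score or of the change from baseline. In 2.18, add that a non-significant primary result will be interpreted from the 95% confidence interval and not taken as evidence that a 4-point effect is absent.

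If a baseline-adjusted primary analysis is adopted to recover power at 80 patients, state the assumed correlation and the power it gives under the stated meaning of the SD.

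The cost is a change of wording and a less favourable power statement; no extra patients are needed. If the sponsor wants to keep 90% power for 4 points with the planned t test, the cost is enrolment of about 156 to 158 patients before any dropout allowance, roughly double the present plan.

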### Statistical analysis

2.18

All data analyses will be accomplished using SPSS software (version 24.0). Continuous data are presented as mean ± standard deviation and categorical data as frequencies. Continuous variables following the normal distribution will be analyzed by Student *t* test; otherwise, nonparametric tests will be used to compare group differences. Statistical test is 2-sided and *P*-value <.05 will be defined as statistically significant. We will adopt multiple imputation to handle missing data statistically. A subgroup analyses will be conducted when necessary. Intention-to-treat approach and last-observation-carried-forward method will be applied to deal with the missing values.

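### The Student t test stated for the primary Cooney outcome carries no baseline covariate; it is valid but gives up precision that a baseline-adjusted model would recover at no cost

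*Protocol article*

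**What the plan says.** Section 2.18 (Statistical analysis) gives one rule for all continuous outcomes: "Continuous variables following the normal distribution will be analyzed by Student *t* test", and a nonparametric test if normality fails. It names no covariate, ANCOVA or mixed model. It adds: "Statistical test is 2-sided and *P*-value <.05 will be defined as statistically significant".

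Section 2.12.1.1 defines the primary outcome as "Cooney wrist score (from baseline to week 4"). Section 2.12.2.1 uses the same form for weeks 2 and 12, and the Discussion describes the score as a before-and-after measure of improvement. Section 2.15 schedules "4 rounds of disease assessments (the baseline, week 2, week 4, and week 12"), so each participant should have a baseline Cooney score.

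Section 2.17 plans 40 per arm for a difference of 4 points, an SD of 7.7 and 90% power. It does not say whether 7.7 is the SD of the score or of its change.

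**The concern.** The question is framed relative to baseline, but the stated test uses the baseline either not at all (week-4 scores) or with a coefficient fixed at 1 (change scores). A regression that estimates the coefficient is at least as precise as either, apart from one degree of freedom.

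Baseline scores can be expected to vary. Section 2.4.1 admits surgical and conservative treatment, any time beyond 6 weeks, and stiffness with or without pain and swelling. Pain alone carries 25 of the 100 Cooney points. Section 2.9 describes a 1:1 list and mentions no stratification, so some chance imbalance with 40 per arm is likely.

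At stake are the width of the confidence interval, the power, and how far the estimate moves with a chance baseline difference. Type I error and unbiasedness are not at stake.

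**Working it through.** **Inputs from the documents.** Alpha: "when *α* = 0.05" (2.17), two-sided (2.18). Target power: "when 1-*β* = 0.90" (2.17). SD: "σ* (standard deviation of 2 groups) = 7.7" (2.17). Effect: "the difference of Cooney wrist score in BTD and placebo group) = 4" (2.17). 40 per arm, 1:1 (2.17).

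**Assumptions.** The correlation r between baseline and week-4 scores is not given, so a range is shown. Baseline and week-4 SDs are taken as equal; neither is given. No dropout.

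**The plan's own figure.** n per arm = 2 × [7.7 × (1.960 + 1.282) / 4]² = 77.9, so 78 per arm and 156 in total. The planned 40 per arm is not reproduced. That is a separate error; here it only sets the starting point.

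**Power of the t test as planned.** Standard error = 7.7 × √(2/40) = 1.72. Noncentrality = 4 / 1.72 = 2.32. With 78 degrees of freedom, power is 63% (non-central t; the normal approximation gives 64%). This holds for whichever variable 7.7 describes.

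**Reading A: 7.7 is the SD of the score.**
- ANCOVA residual SD = 7.7 × √(1 − r²), 77 degrees of freedom.
- SD of change = 7.7 × √(2(1 − r)), 78 degrees of freedom.

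| r | ANCOVA SD | ANCOVA power | Change SD | t test on change | t test on week 4 |
|---|---|---|---|---|---|
| 0.3 | 7.35 | 67% | 9.11 | 49% | 63% |
| 0.5 | 6.67 | 75% | 7.70 | 63% | 63% |
| 0.6 | 6.16 | 82% | 6.89 | 73% | 63% |
| 0.7 | 5.50 | 89% | 5.96 | 84% | 63% |

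**Reading B: 7.7 is the SD of change.** ANCOVA residual SD = 7.7 × √((1 + r)/2). The t test on change stays at 63%.

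| r | ANCOVA SD | ANCOVA power |
|---|---|---|
| 0.3 | 6.21 | 81% |
| 0.5 | 6.67 | 75% |
| 0.6 | 6.89 | 73% |
| 0.7 | 7.10 | 70% |
| 0.8 | 7.30 | 68% |
| 0.9 | 7.51 | 65% |

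**Chance imbalance.** If the arms differ at baseline by D and the true slope is b, the week-4 comparison is shifted by b × D and the change comparison by (b − 1) × D. As an illustration under reading A with r = 0.5, equal SDs give b = 0.5. A baseline difference of one standard error (1.72 points) then shifts the week-4 estimate by +0.86 and the change estimate by −0.86, against a target difference of 4. ANCOVA estimates b and removes the linear shift on average.

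**Can adjustment rescue 80 patients?** Under reading A, ANCOVA reaches 90% power with 40 per arm only at r of about 0.71 (0.70 by the normal approximation) and with no dropout. Under reading B it does not reach 90% at any r shown.

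**The case against.** - **The t test is valid.** It keeps its type I error and is unbiased under randomisation. This stands: the point concerns efficiency, not a wrong test.
- **The change-score reading already uses baseline.** A reader might infer that chance imbalance goes wholly uncorrected. The documents do not support that. The definitions in 2.12.1.1 and 2.12.2.1 and the Discussion point to change scores, for which imbalance is over-corrected when the slope is below 1. Only a test on week-4 scores would leave it uncorrected.
- **The gain is unknown and may be small.** This stands. Neither r nor the meaning of 7.7 is given. If 7.7 is the SD of change and r is 0.9, ANCOVA adds about 2 points (63% to 65%).
- **A general rule that change scores lose to week-4 scores below r = 0.5 is not established.** This stands. The threshold is half the ratio of baseline SD to week-4 SD: 0.35 for a ratio of 0.7 and 0.65 for a ratio of 1.3. It is 0.5 only when the SDs are equal.
- **The low power comes from section 2.17.** This stands; the shortfall should not be counted again as the weight of this point.
- **An unseen analysis plan might adjust for baseline.** This carries little weight. The article states a test, with a rule for replacing it, and a plan that followed that text would be unadjusted.

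**Conclusion.** The point holds as a recommended efficiency improvement, ranked below the sample-size error. The stated method for the primary outcome omits a covariate that the trial will already hold. At every r shown and under both readings of 7.7, ANCOVA has at least the power of the t tests it was compared with. The gain over the better t test under reading A runs from about 4 points (67% against 63% at r = 0.3) to 12 points at r = 0.5, and is about 5 points at r = 0.7. Under reading B, the gain over the change-score test falls from about 18 points at r = 0.3 to about 2 at r = 0.9. These sizes rest on assumed correlations, equal baseline and week-4 SDs, and complete data.

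A reader might also infer that the planned analysis is biased, or that adjustment would restore the planned 90% power. The documents support neither.

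**What to change.** In section 2.18, and in the analysis plan if there is one, name the primary analysis before unblinding: a linear model of week-4 Cooney score on treatment group and baseline Cooney score, reporting the adjusted mean difference with its 95% confidence interval and two-sided p value. For this outcome it should replace both the t test and the switch to a nonparametric test after a normality check, so that a single method governs the primary result. Use the same form, each with its own baseline, for Cooney at weeks 2 and 12, PRWE and the SF-36 scales.

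The cost is a change of wording. SPSS, already named in 2.18, fits the model, and no extra visits, data or patients are needed. The sample size in 2.17 must still be corrected separately, and the two missing-data methods named together in 2.18 (multiple imputation and last observation carried forward) are not settled by this change.

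### The observed distribution decides whether the primary Cooney comparison is a t test or an unnamed nonparametric test, so its effect measure is not fixed in advance

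*Protocol article*

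**What the plan says.** The rule in section 2.18 (Statistical analysis) has two branches. The first is "Continuous variables following the normal distribution will be analyzed by Student *t* test". The second is "otherwise, nonparametric tests will be used to compare group differences". Significance is judged by one statement for all tests: "Statistical test is 2-sided and *P*-value <.05 will be defined as statistically significant". The same section presents continuous data as mean and standard deviation, and plans multiple imputation for missing values.

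The primary outcome (section 2.12.1.1) is the Cooney wrist score from baseline to week 4. It is a continuous total: "The total score of Cooney is 100 points". Neither that section nor 2.18 names a separate primary analysis.

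Section 2.17 sizes the trial on "the difference of Cooney wrist score in BTD and placebo group) = 4", with a standard deviation of 7.7, a margin of 0, and 40 patients per group.

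**The concern.** Whether the Cooney score follows a normal distribution can only be judged from the trial's own data. Under 2.18 the primary comparison is therefore settled after the data exist.

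The two branches do not report the same thing. A t test comes with a difference in means, in Cooney points, that can be set against the 4 points in 2.17. A rank test, the usual nonparametric choice, asks whether scores in one group tend to exceed those in the other, and its p value carries no estimate of the mean difference. The article would still present means and standard deviations, so in that branch the displayed summary and the p value could answer different questions.

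Multiple imputation adds a practical gap. The normality verdict could differ between imputed data sets, and the section does not say how a nonparametric result would be combined across them.

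At stake is whether the headline result answers the question the trial was sized for, and whether a borderline result can be challenged because another test would have given another verdict.

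**Working it through.** **Inputs from the article.** Difference 4, SD 7.7, alpha 0.05, power 0.90, allocation 1:1, 40 per arm (sections 2.9 and 2.17); two-sided testing (2.18).

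**Assumptions, not in the article.** Normality is checked by Shapiro-Wilk at 0.05 in each arm. If both arms pass, the t test is used; otherwise Mann-Whitney. The scores are normal, mildly skewed (gamma, shape 8) or strongly skewed (gamma, shape 2). All are scaled to SD 7.7 and differ between arms only by a shift.

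**1. The plan's own figure.** The usual two-mean formula gives n per arm = 2 × (1.960 + 1.282)² × 7.7² / 4² = 2 × 10.507 × 59.29 / 16 = 77.9, so 78 per arm and 156 in total. The stated 80 is not reproduced. That is a separate matter, but it sets the power here. At 40 per arm the standard error of the mean difference is 7.7 × √(2/40) = 1.72 and 4/1.72 = 2.32. Two-sided power is Φ(2.32 − 1.96) = 0.64, or 0.63 with the t distribution. All of these quantities belong to a comparison of means.

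**2. Switching when the data are truly normal.** If each arm has a 5% chance of failing the check, the chance that at least one fails is 1 − 0.95² = 9.75%.

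**3. Simulation, 40 per arm, 10,000 trials per cell.**

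| Assumed distribution | Rank test chosen | Type I error of the rule | Tests disagree, no difference | Tests disagree, difference 4 | Power, t test | Power, Mann-Whitney |
|---|---|---|---|---|---|---|
| Normal | about 10% | 0.051 | 2% | 7% | 0.63 | 0.61 |
| Mild skew | about 55% | 0.049 | 2% | 8% | 0.63 | 0.64 |
| Strong skew | about 99% | 0.049 | 3% | 15% | 0.65 | 0.78 |

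The disagreement columns give the share of trials in which the choice of test decides whether the result is significant. They are not the share in which the rule misleads. If the test were picked after both p values had been seen, type I error would be about 0.055 to 0.065. Nothing in the article suggests that this is intended.

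**4. Effect of fixing a baseline-adjusted mean difference.** If 7.7 is the SD of the week 4 score and r is its correlation with the baseline score, the residual SD is 7.7 × √(1 − r²). For r = 0.3 this is 7.35 and power at 40 per arm is 0.67. For r = 0.7 it is 5.50 and power is 0.89. Without adjustment it is 0.63. The article gives no r, so the range is an assumption.

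**The case against.** The strongest reply is that this is a common rule, stated in advance and harmless for error control. The simulation bears that out. A reader might infer that the switch inflates the false-positive rate, but applied mechanically it keeps it at about 0.05. The 10% in the normal case is a rate of changing method, not of changing the conclusion.

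A second reply is that an unshown analysis plan may name the normality criterion and the exact test. That is fair, and the absence of those details is not the point. The switch itself is written into 2.18, and a later plan could remove it only by departing from the article.

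A third reply is that under a pure shift a rank test addresses the same shift, and a Hodges-Lehmann estimate would express it in Cooney points. This is correct, but the article specifies neither a shift model nor such an estimate.

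Three stronger readings are tempting and are not supported:

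- **That the wrong distribution is checked.** The article does not say that a pooled raw distribution is examined. For two groups, checking within each arm is equivalent to checking residuals.
- **That a bounded 0 to 100 score must fail normality more often.** Bounds matter only if scores lie near them. No expected Cooney mean is given, and summing four parts tends to bring a total closer to normal.
- **That rank results cannot be pooled over imputations.** A rank-based effect with a standard error, such as the Mann-Whitney probability, can be pooled. The fair statement is that 2.18 does not say how.

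**Conclusion.** The concern holds as a weakness in how the primary analysis is fixed, not as an error-rate problem. Section 2.18 leaves both the test and the effect measure for the primary outcome to the observed distribution, whereas 2.17 plans for a mean difference of 4 points.

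The size is moderate. With a real 4-point difference, the choice of test would decide significance in about 7% of trials if scores are normal and about 15% if they are strongly skewed. With no difference it would do so in 2% to 3%. These percentages rest on the assumed Shapiro-Wilk rule and distributions. The conclusion that the effect measure is not fixed rests on the text alone. The rule should be changed, but it would not by itself invalidate the trial.

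**What to change.** In section 2.18, state one primary analysis that applies whatever the distribution: the between-group mean difference in week 4 Cooney score, with its 95% CI, from a linear model adjusted for baseline Cooney score. Keep a rank-based or bootstrap analysis as a labelled sensitivity analysis.

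The model yields an estimate and standard error that pool directly over imputations. It also settles whether the outcome is the week 4 score or the change, because with baseline in the model both give the same treatment difference. The adjustment goes beyond what removing the switch requires, but it uses a score already collected and recovers some of the power that is short at 40 per arm.

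The cost is one sentence and no extra data. The downside is some loss of power relative to a rank test if scores are strongly skewed: 0.65 against 0.78 in the unadjusted simulation.

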## Introduction

1

Distal radius fracture (DRF) is an increasingly common upper limb injury. A certain percentage of complications occur frequently after fracture healing regardless of surgical or conservative treatment. Common complications include wrist instability, stiffness, nonunion, tendon irritation, infection, and local pain syndrome.^[1,2]^ Wrist stiffness is one of the most common and difficult sequela to treat, up to 30% of DRF patients.^[3]^ Manipulation is an effective treatment method, but there are problems such as intense pain, swelling and long treatment periods.^[4]^ Therefore, a combinative therapeutic strategy that could relieve pain, swelling and joint adhesion is necessary to benefit DRF patients after surgeries.

In recent years, traditional Chinese medicine (TCM) has played an important role in the rehabilitation of various kinds of fractures and arthritis. Research suggests TCM has analgesic and anti-inflammatory effects in patients with osteoarthritis.^[5]^ TCM also could relieve pain and swelling after fractures ^[6]^ and promote fracture healing in multi-regulatory pathways, such as Wnt/β-catenin, bone morphogenetic protein/Smad and mitogen-activated protein kinase pathway.^[7]^

Shi's Yi-Qi Bu-Shen Tong-Luo decoction (BTD) is a century-old historical TCM prescription, including Astragali Radix, Radix Angelicae Sinensis, Flos Carthami, Rhizoma Chuanxiong, Taxilli Herba, Eucommiae Cortex, Epimedii Folium, Olibanum, Stephaniae Tetrandrae Radix (details in Table 1). It has been used to improve joint pain and swelling in the DRF late stage in clinical treatment for decades. According to the TCM theory, BTD could supplement Qi and activate blood circulation, then promote release of adhesion and recovery of joint function.^[8,9]^ Unfortunately, its efficacy remains unverified with rigorous research and exact data.

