#### Inclusion criteria

2.4.1

Participants meeting the following criteria will be included.

(1)patients with diagnosis of DRF and age from ≥18 and ≤75(2)receive conservative treatment (such as plaster external fixation, small splint fixation and external fixation stent) or surgery(3)over 6 weeks after the fractures at least, X-ray shows blurred fracture line and well callus growth, external fixation such as plaster and support is removed(4)wrist stiffness, with or without swelling, pain, range of joint activities is significantly lower than the healthy side(5)able to understand and sign the informed consent and ensure compliance

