### Visiting plan

2.8

At baseline (Visit 1), patients begin to receive manipulation plus BTD or BTD placebo and laboratory tests. Patients will visit again at week 2 and 4 (Visit 2 and 3) and perform laboratory tests at week 4. Both Medicine and manipulation intervention will be finished at week 4. Then the follow-up visit (Visit 4) will be taken at week 12. Every patient should visit and do laboratory tests within 3 days after the original time point (details in Table 2). During the study period, all the treatments and drugs patients have used should record in details in CRFs.

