### Safety assessments

2.13

To assure the safety of participants, the adverse effects will be reported and analyzed. At baseline and after BTD intervention, patients’ kidney and liver function will be tested. Additionally, side effects of TCM herbs will be record along the trial, such as gastrointestinal reaction, abdominal pain, dizzy, rash, and and so on. Participants were free to withdraw from the study at any time. The data collection process will be administered by the project director.

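### Section 2.18 prescribes both multiple imputation and LOCF for the same missing values without ranking them, so the primary week-4 result is not uniquely defined, and LOCF suits a recovering population poorly

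*Protocol article*

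**What the plan says.** Section 2.18 (Statistical analysis) makes two commitments on missing data. The first is: "We will adopt multiple imputation to handle missing data statistically". Two sentences later comes: "Intention-to-treat approach and last-observation-carried-forward method will be applied to deal with the missing values". Both are unconditional, and no other section assigns either method to an outcome, a visit or a role.

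The primary outcome (2.12.1) is the change in the Cooney wrist score from baseline to week 4, on a scale where "The higher Cooney score, the better recovery of wrist function". The only earlier scores available to carry to week 4 are those at baseline and week 2 (2.8, Visiting plan).

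On the expected course, both arms receive manipulation, of which the Introduction says: "Manipulation is an effective treatment method". Patients enter at least 6 weeks after fracture, when "X-ray shows blurred fracture line and well callus growth, external fixation such as plaster and support is removed" (2.4.1). On missing values, 2.13 notes: "Participants were free to withdraw from the study at any time". No expected dropout rate is given.

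**The concern.** A missing week-4 Cooney score cannot be both carried forward and multiply imputed in a single primary analysis. With no ranking, two primary estimates and two P-values satisfy the plan, and nothing in the article fixes the choice before the data are examined.

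The two methods are also not interchangeable in this trial. LOCF assumes no change after the last visit. The article's own description points to rising scores in both arms, so a carried value sits below what the patient would probably have reached. It is also analysed as if it had been observed. What this does to the difference between arms depends on who drops out, when, and how much recovery is lost.

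**Working it through.** **1. The text.** Both sentences concern missing data in general and neither is qualified. The conflict therefore needs no arithmetic and no assumption about dropout.

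**2. Inputs for the size of the LOCF effect.**
- From 2.17: SD 7.7, design difference 4, 40 per arm. From 2.18: two-sided test at 0.05.
- Assumed, because the article gives none of them: placebo gain g from baseline to week 4 of 5, 10 or 20 points; half of each gain, and half of any treatment effect, reached by week 2; half of dropouts leaving before week 2 (baseline carried, whole gain lost) and half after (week 2 carried, half the gain lost); dropout unrelated to the score.

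Section 2.18 states no figure that could be reproduced. With complete data, 40 per arm gives about 63% power for 4 points at SD 7.7. That this is below the planned 90% is a separate sample-size matter and plays no part here.

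**3. Expected LOCF difference.** The average share of gain lost per dropout is 0.5 × 1 + 0.5 × 0.5 = 0.75. With true effect δ and dropout shares d_B (BTD) and d_P (placebo):

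E(difference) = δ − 0.75·d_B·(g + δ) + 0.75·d_P·g

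- No effect, d_B = 10%, d_P = 20%: 0.75 × 0.10 × g = 0.375, 0.75 and 1.5 points for g = 5, 10, 20. The sign reverses if the rates are swapped.
- δ = 4, d_B = 20%, d_P = 10%, g = 5: 4 − 0.15 × 9 + 0.075 × 5 = 3.0. For g = 10: 4 − 0.15 × 14 + 0.075 × 10 = 2.65. For g = 20: 4 − 0.15 × 24 + 0.075 × 20 = 1.9.
- δ = 4, rates swapped (10% BTD, 20% placebo), g = 20: 4 − 0.075 × 24 + 0.15 × 20 = 5.2.
- δ = 4, 10% in both arms: 4 − 0.075 × 4 = 3.7, whatever g is.
- No effect, equal dropout: 0.

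**4. Effect on the test.** Carried values also widen the spread. In an arm with gain G and dropout d, the variance is 7.7² + 0.625·d·G² − 0.5625·d²·G².

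For g = 20 with no effect and dropout of 10% and 20%, the added variances are 25 − 2.25 = 22.75 and 50 − 9 = 41. The standard error is √((2 × 59.29 + 22.75 + 41)/40) = 2.135, the shift is 1.5/2.135 = 0.70 standard errors, and about 10.7% of null trials reject. For g = 5 the same steps give 0.375/1.75 = 0.21 standard errors and about 5.5%.

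Simulation of 6000 trials per scenario (correlations 0.6, 0.5 and 0.7 between baseline–week 2, baseline–week 4 and week 2–week 4) agrees within simulation error:

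| Assumed gain | Null shift, 10% v 20% | Type I error | Mean estimate, true 4, 20% BTD v 10% placebo | Power, true 4, 10% both arms |
|---|---|---|---|---|
| 5 | 0.4 | about 5.5% | 3.0 | about 55% |
| 10 | 0.75 | about 7% | 2.6 | about 51% |
| 20 | 1.5 | about 10.5% | 1.9 | about 42% |

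The fair reference for the last column is about 58%, the power of completers alone at 10% dropout. The part due to LOCF is therefore 58 − 55 = 3 to 58 − 42 = 16 percentage points.

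**5. Does the choice of method matter?** A separate simulation (1000 trials per scenario, gain 10, week 2 always carried, true difference 4) compared the methods directly. Multiple imputation averaged 3.9 to 4.1 throughout. LOCF averaged 3.7 with 10% or 20% missing in both arms, 2.9 with 20% on BTD and 5% on placebo, and 4.7 with those rates swapped. The two methods disagreed on significance in about 9% to 23% of trials. Those imputation P-values used a normal reference, and 6.4% to 6.6% of null trials rejected, so a little of the disagreement comes from that cut-off and not from the estimates.

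**The case against.** The strongest defence is that a journal article condenses the plan and that an unseen analysis plan may name one method as primary. That would excuse silence. It does not excuse two unqualified commitments that conflict as written.

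The defence is right on size. Neither dropout nor gain is documented, and at a small gain or a small imbalance the distortion is minor. Several stronger readings are tempting, and the document does not support them:

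- A reader might infer that the method could be chosen unblinded. Section 2.10 keeps the analysing statisticians unaware of allocation until the trial is complete. What stands is that the choice could follow sight of the data.
- A reader might infer that LOCF is biased whenever dropout rates differ. Timing and lost gain also matter and can offset unequal rates. Under equal dropout, timing and gain with no true effect, there is no bias.
- A reader might take a type I error near 10% as the expected harm. It needs a gain of about 20 points together with a 10-percentage-point dropout imbalance.
- A reader might charge LOCF with the whole fall in power from 63%. Any 10% dropout costs part of that.
- A reader might object that intention-to-treat is listed as a missing-data method. The sentence can equally mean that all randomised patients are kept and LOCF fills the gaps, so this is wording and not a further defect.

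Multiple imputation is not a cure-all either. The simulations let dropout be unrelated to outcome. If patients leave because of adverse reactions or lack of effect in ways the recorded scores do not capture, imputation can be biased too.

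**Conclusion.** The concern holds on two counts. First, the plan allows two different primary week-4 results and does not say which one counts; this rests on the text alone. Second, LOCF is a poor candidate for the primary role, because it understates week-4 scores in patients expected to improve in both arms. The direction of its effect on the difference is fixed only under equal dropout and timing, where it pulls a true effect towards zero.

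The numerical size is conditional on assumed gains of 5 to 20 points, the assumed dropout patterns and linear recovery. Within that range it runs from negligible to more than a third of the 4-point design difference (1.5/4 = 38%). It should be read as a range and not as a prediction.

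**What to change.** Replace the two missing-data sentences in 2.18 with a single rule. The primary analysis includes all randomised patients in their assigned group. Missing Cooney scores are multiply imputed using baseline and all available follow-up scores, with results pooled by Rubin's rules. Either delete LOCF or label it a sensitivity analysis that cannot replace the primary result. Any check on the missing-at-random assumption belongs in the same sensitivity role.

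The cost is two sentences, settled before anyone examines outcome data. Multiple imputation is already planned, and no visit, treatment or sample-size provision changes.
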